### Primary Outcomes

#### Effects of Video Game Training on Attentional Networks: Behavioral and Electrophysiological Results

##### Oddball Task

The capacity to suppress irrelevant information and to concentrate on the relevant task [86] is negatively affected by aging. The question is whether the effects of training with cognitive video games are transferable to untrained tasks (transfer effect). Despite the great appeal of video games as a way to improve perceptual and cognitive abilities, evidence of their efficacy is mixed [49,50,52,64,87-88]. However, the results of several recent meta-analytic studies [59-62] suggest that video game training can be moderately effective in healthy older adults but that its positive effects are moderated by several variables including the complexity of the games, the age of the participants, the duration of the training program, and the cognitive processes assessed.

Previous studies indicate that deviance distraction occurs because deviant sounds violate the cognitive system’s expectations [89]. Attention capture has been studied from an electrophysiological perspective; the distractor is characterized by a pattern of 3 brain responses [90,91]: (1) mismatch negativity (MMN) and enhanced N1 when the distractor deviates considerably from the repetitive background, (2) P3a (novelty P3), and (3) RON. The MMN response reflects the preattentive detection of an unexpected change in the auditory context and results from the comparison between a memory trace for past acoustic stimuli and the current auditory signal [92]. The P3a response represents the involuntary orientation of attention toward the novel sound [93] and results from an attentional interruption involving frontal areas [94]. RON is also observed when participants are performing a primary task and must redirect their attention toward that task [95]. In this RCT, we undertake electrophysiological recordings to explore the underlying neural mechanisms of successful transfer of training to attentional performance in the oddball task. We expect that the cognitive video game–trained group will improve both the ability to return attention to the relevant task after having been distracted by the novel stimulus (RON) and the ability of the brain to pay attention to the novel stimulus (P300). In our lab, we previously investigated the effect of novelty in young adults using a haptic oddball paradigm consisting of processing textured surfaces [96]. We do not expect this pattern of results in the active control group and thus predict a group × session interaction.

##### Stroop and Negative Priming Task

Cognitive processes that involve top-down control mechanisms decline with aging but more automatic processes do not [20,22]. The Stroop interference effect reflects the extra time needed to resolve the conflict generated by the irrelevant word meaning in the incongruent condition. One view is that suppression processes relying on executive control are engaged in preventing the irrelevant dimension from taking control of the response [97]. In this study, we investigate the effect of training older adults with nonaction video games on inhibition processing using both behavioral and electrophysiological responses. The task has been designed to assess training-related behavioral and neural changes in Stroop interference and in negative priming (NP). NP (a measure of distractor inhibition) and the standard Stroop effect are assessed in the same task. In the standard NP procedure, participants are presented with pairs of prime and probe displays containing 2 stimuli, the to-be-responded target and the to-be-ignored distractor. In the critical trials, participants must respond to a target that served as a distractor in the previous prime display (the ignored repetition condition). The common finding is that reaction times to targets in the ignored repetition condition are slower than in the control condition, in which the distractor in the prime display is not repeated as the target in the probe display [98-101]. The aim is to investigate whether training older adults improves control, effortful inhibition (Stoop interference), to a greater extent than automatic passive inhibition (NP). The experimental task uses ERPs in combination with the Stroop and NP before and after training to examine the neural correlates of inhibition [102]. Responses for the Stroop analysis will be coded as a function of the congruency between the color and the meaning of the stimulus. Congruent trials are those in which the color of the word coincides with the color in which it is presented. Incongruent trials are those in which the color word does not coincide with the color in which it is displayed. We will also code trials according to the congruency of the previous trial (N−1) in order to compute the NP effect for each trial. The design for the NP effect consists of Group (younger, older adults), Session (pretraining, posttraining, follow-up), and Type of intervention (experimental, active control) as between-participants factors and Repetition (ignored repetition and control) as within-participants factors. Responses for NP analyses will be coded as a function of the relationship between the color of the current target word and the color denoted by the word in the previous trial (distractor). Thus, the ignored repetition trials are those in which the word in the preceding trial denoted the color of the word of the current stimulus. Control trials are those in which both the target (color) and the distractor (word) in the current trial are different from the target and distractor in the previous trial. The ignored repetition condition is always an incongruent trial preceded by an incongruent trial. The aim is to investigate whether the Stroop interference effect in older adults decreases after training while NP does not change. An important addition to the behavioral measures will be the ERP recording while performing the task before and after training to investigate brain activity changes after training.

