**Methods:**

A single-blinded randomized controlled trial with an experimental group and an active control group, pretest, posttest, and 6-month follow-up repeated measures design is used in this study. A total of 75 cognitively healthy older adults were randomly distributed into experimental and active control groups. Participants in the experimental group received 16 1-hour training sessions with cognitive nonaction video games selected from Lumosity, a commercial brain training package. The active control group received the same number of training sessions with The Sims and SimCity, a simulation strategy game.

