## Methods

### Overview of the Study Design

A 2-arm, parallel-design RCT [72] was designed to evaluate the effectiveness of video game training to promote cognitive and brain health in older adults. Figure 1 shows the Consolidated Standards of Reporting Trials flow diagram of the study. This RCT is being conducted in Madrid, Spain, with an allocation ratio of 1:1 to evaluate the influence of training with nonaction video games on attention and memory functions. The design was a single-blind design. Eligible participants were randomized using a computer algorithm into intervention (cognitive nonaction video game training) or active control (life-simulation games) groups. Researchers were not blind to treatment allocation. The Universidad Nacional de Educación a Distancia (UNED) Institutional Review Board approved the study protocol. All participants provided written informed consent.

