### Participants

Participants were randomly assigned to 1 of the 2 parallel groups, either the intervention video game training group or the active control group (see Figure 1). The pretest, posttest, and 6-month follow-up assessments are conducted at the UNED Department of Basic Psychology II by one of the authors with the assistence of other members of the group. The training sessions were carried out at the UNED Associate Center, Escuelas Pías, Madrid, and lasted 8 to 10 weeks. A total of 138 participants were recruited from flyers, advertisements, by word of mouth, and from UNED’s special program for the elderly screened for eligibility. Finally, 75 older adults (age range 55 to 84 years) met the requirements for participation in the study and signed the consent form and were randomly assigned to the experimental or the active control groups before carrying out the laboratory tasks. The 2 groups do not differ significantly in age, years of education, global cognition, depression, memory, or verbal abilities.

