## Results

All analyses will be performed with the SPSS (IBM Corp) program. Statistical significance is considered as a *P* value of <.05. Analyses of variance will be conducted with 2 groups (experimental and active control) at 3 time points (pretest [baseline], posttest [postintervention], and follow-up [after 6 months without contact]). Electrophysiological data will be analyzed using EEGLAB/ERPLAB.

The preparatory phase for using the games has been completed. License to use the games has been granted by Lumosity. Participants have been recruited, pretested, and trained. The final results from this RCT are expected by the end of 2017.

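### The negative-priming analysis lists Session as a between-participants factor and adds a younger/older factor, which contradicts the trial's repeated-measures design in older adults only

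*Protocol article*

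**What the plan says.** In the protocol article, under Primary Outcomes, the Stroop and Negative Priming Task section sets out the design for the NP effect. It names "Group (younger, older adults), Session (pretraining, posttraining, follow-up), and Type of intervention (experimental, active control) as between-participants factors", followed by "Repetition (ignored repetition and control) as within-participants factors". No other sentence in the article gives the factors for this measure.

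The rest of the article describes a different structure:

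- Overview of the Study Design: "A 2-arm, parallel-design RCT [72] was designed to evaluate the effectiveness of video game training".
- Participants: "75 older adults (age range 55 to 84 years) met the requirements for participation in the study".
- Abstract, Methods: "A total of 75 cognitively healthy older adults were randomly distributed into experimental and active control groups", and a "pretest, posttest, and 6-month follow-up repeated measures design is used in this study".
- General Procedure: the main question is whether arm interacts with testing session, and recordings are made at T1, T2 and T3.
- Results: "Analyses of variance will be conducted with 2 groups (experimental and active control) at 3 time points".

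**The concern.** Two of the three factors listed as between participants do not fit the trial. Nobody in it belongs to a younger-adult group, and Session does not divide people into separate sets because the same people return each time.

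The placing of Session decides the error term. With Session between participants, the stable differences between people stay in the error against which change over sessions is tested, although they cancel when each person is compared with themselves. Tests of change then lose sensitivity. Tests of the average difference between arms gain false precision, because three records per person count as three people.

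The direction matters for this measure. The section asks whether Stroop interference falls after training while NP stays the same. A test that seldom rejects makes an apparent absence of change in NP more likely, whether or not training affects it.

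**Working it through.** **Step 1: the texts compared.**

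| Feature | NP design sentence | Rest of the article |
|---|---|---|
| Age groups | younger and older | older adults only, 55 to 84 years |
| Session | between participants | repeated measures, T1, T2, T3 |
| Groups | age group and arm | two arms |
| Within-participants factors | Repetition only | time points repeated within person |

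The contradiction needs no arithmetic. The Group factor has one populated level, so neither its main effect nor any interaction with it can be estimated.

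**Step 2: inputs for the consequence of the Session error.** The plan gives no figure to reproduce here.

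- Participants left at posttest (Sample Size section): 38 − 8 = 30 and 37 − 12 = 25, total 55.
- Alpha 0.05 (Sample Size section).
- Response: the NP effect per person and session (ignored repetition minus control), variance set to 1. On this scale, arm x Session for the NP effect is the Intervention x Session x Repetition term of the full model.
- r, the correlation of the NP effect between two sessions in the same person. The article gives none. **Assumed: 0.3, 0.5, 0.7.**
- For the three-session figures, all 55 are assumed to stay to follow-up, with equal correlation between sessions.

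**Step 3: pre-post contrast between arms (1 df, normal approximation).** The variance of a person's change is 2(1 − r). Treated as independent records it is taken as 2. The standard error is therefore too large by 1/√(1 − r), and the real type I error is P(|Z| > 1.96/√(1 − r)). For power, assume an arm difference of 0.5 SD. The true standard error is √[2(1 − r)] × √(1/30 + 1/25) = √[2(1 − r)] × 0.271.

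| r | SE ratio | Real type I error | Power, Session within | Power, Session between |
|---|---|---|---|---|
| 0 | 1.00 | 5% | – | – |
| 0.1 | 1.05 | 3.9% | – | – |
| 0.3 | 1.20 | 1.9% | 34% | 22% |
| 0.5 | 1.41 | 0.6% | 45% | 18% |
| 0.7 | 1.83 | 0.03% | 66% | 12% |

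Example at r = 0.5: the true standard error is 1 × 0.271, so 0.5/0.271 = 1.85. The critical value is 1.96 if Session is within and 1.96 × 1.41 = 2.77 if it is between. Power is P(Z > 0.11) = 45% and P(Z > 0.93) = 18%.

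**Step 4: the three-session interaction (2 df).** Between participants, there are 3 × 55 = 165 records and 3 × (55 − 2) = 159 error df. Within participants, there are 2 × (55 − 2) = 106 error df. In 20,000 simulated null data sets per setting, the between version rejected in 1.5%, 0.3% and under 0.1% at r = 0.3, 0.5 and 0.7. The within version rejected in about 5% throughout. With an arm difference of 0.5 SD at both posttest and follow-up, approximate power is 34%, 45% and 68% (within) against 18%, 12% and 5% (between).

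**Step 5: the intervention main effect.** The average of three sessions has variance (1 + 2r)/3, but treating the records as independent assumes 1/3. The real type I error is about P(|Z| > 1.96/√(1 + 2r)). At r = 0.3, 0.5 and 0.7 the cut-offs are 1.55, 1.39 and 1.27, giving about 12%, 17% and 21%. The simulation gave 12%, 17% and 20%.

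At r = 0 both versions held 5% in the simulation, so the distortion comes only from ignoring the repeated measures.

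**The case against.** The strongest reply is that this is a slip of the pen. The abstract, General Procedure and Results all describe the correct design, and the NP section itself speaks of training older adults. An analyst who sets up the usual repeated-measures model will never meet these error rates. That it is a slip is probable, and the consequences above do depend on the sentence being followed literally. The general statements nevertheless contradict the NP sentence without correcting it, and that sentence is the only factor specification for this measure. A specific statement would normally govern, and a conflict left open lets the model be chosen once data are in hand.

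The reply is also right that the size is uncertain. NP is a difference score, so its cross-session correlation may be below 0.3. At r = 0.1 the type I error is 3.9%, a small loss.

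A reader might infer more than the text supports:

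- *That the model cannot be run.* The empty Group level would simply drop out. What remains runs, with the wrong error term.
- *That a primary task, or the trial, is analysed wrongly.* The sentence covers the NP effect only. Stroop interference, from the same task, is outside it, and the hypotheses under Objectives and Hypotheses name Stroop, not NP.
- *That the trial plans to conclude NP is unchanged.* The text presents this as a question to investigate, not a planned conclusion.
- *That younger means the younger part of 55 to 84 years.* No cut-off or subgroup is defined, and the Session error would remain.

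**Conclusion.** The point stands for the NP effect within the Stroop-negative priming task. The stated factor structure contradicts the trial's own design in two places: an age-group factor with an empty level, and a repeated factor declared as between participants. This follows from the text alone.

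The statistical consequence is conditional on literal use of the sentence. For any positive cross-session correlation, tests involving Session are too conservative and the test of the intervention main effect is anti-conservative. The directions are firm; the sizes are illustrations that rest on the assumed r, the 0.5 SD effect and the numbers at posttest. The pre-post and three-session figures differ because they test different contrasts. It is more than a clerical matter, since the sentence fixes the error term and the error leans towards one half of the pattern being investigated.

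**What to change.** Replace the NP design sentence with wording such as: *Negative priming is analysed with Type of intervention (two arms) between participants, and with Session (three occasions) and Repetition (two levels) within participants; the test of interest is Intervention x Session x Repetition.* Delete the younger/older Group factor.

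The cost is one sentence. No data collection, sample size or staffing changes. The article places data analysis in 2017, after the assessments it describes as still under way, so the correction could be made and dated before the NP data are analysed.

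### Negative-priming control trials are not restricted to incongruent trials although ignored-repetition trials are, so the priming score as defined includes a share of Stroop interference

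*Protocol article*

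**What the plan says.** All the relevant text is in the protocol article, Primary Outcomes, Stroop and Negative Priming Task.

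- One stream of trials serves both measures: "NP (a measure of distractor inhibition) and the standard Stroop effect are assessed in the same task".
- Congruent trials are in that stream: "Congruent trials are those in which the color of the word coincides with the color in which it is presented".
- Incongruent trials are slower by definition: "The Stroop interference effect reflects the extra time needed to resolve the conflict generated by the irrelevant word meaning in the incongruent condition".
- Ignored repetition is coded from the preceding word: "the ignored repetition trials are those in which the word in the preceding trial denoted the color of the word of the current stimulus". A separate sentence adds a restriction: "The ignored repetition condition is always an incongruent trial preceded by an incongruent trial".
- The control rule is: "Control trials are those in which both the target (color) and the distractor (word) in the current trial are different" from those of the previous trial. No congruency restriction is attached to it.
- The NP design has one within-participants factor, Repetition, with the levels ignored repetition and control. Congruency of the scored trial is not a factor.
- The stated aim is to find out "whether the Stroop interference effect in older adults decreases after training while NP does not change".

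**The concern.** NP is the reaction time on ignored-repetition trials minus that on control trials. The difference measures priming only if the two trial types are alike in everything else that affects reaction time. Here one type is always incongruent, while the other may be congruent. A word in red ink reading red, after a word in green ink reading blue, passes the control rule.

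The interference cost is therefore carried by all ignored-repetition trials and by only some control trials, and part of it enters the NP score. The analysis is meant to show that training changes one effect and leaves the other alone. If the second score contains a fraction of the first, a pure change in Stroop interference moves both.

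**Working it through.** The article states no figure on this point, so there is none to reproduce. The check has two parts.

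**1. What the score measures**

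Let S be Stroop interference (incongruent minus congruent reaction time) and q the share of control trials that are congruent. Previous-trial effects are set aside.

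- Mean control time = (1 − q) × incongruent control time + q × congruent control time = incongruent control time − q × S.
- Measured NP = ignored-repetition time − mean control time = true NP + q × S.
- With q constant over sessions, change in measured NP = change in true NP + q × change in S.

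**2. How large q could be**

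Assumptions, none of them in the article: K colours, a proportion p of congruent trials, trials drawn independently at random, and colours and words equally frequent. Under the rule as written, with no colour or word shared with the previous trial, the weights of eligible control trials are:

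- congruent after congruent: p × p(K − 1)/K
- congruent after incongruent: (1 − p) × p(K − 2)/K
- incongruent after congruent: p × (1 − p)(K − 2)/K
- incongruent after incongruent: (1 − p) × (1 − p)(K − 2)(K − 3)/[K(K − 1)]

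For K = 4 and p = 0.25, in the same order, these are 0.0469, 0.0938, 0.0938 and 0.0938, in total 0.3281. So q = 0.1406/0.3281 = 0.43, and the incongruent-after-incongruent share is 0.0938/0.3281 = 0.29. For K = 4 and p = 0.50 they are 0.1875, 0.1250, 0.1250 and 0.0417, in total 0.4792. So q = 0.3125/0.4792 = 0.65, and the incongruent-after-incongruent share is 0.09.

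Enumerating all pairs of previous and current trials gives these values of q at p = 0.25 and p = 0.50:

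| Colours | Any previous trial | Previous trial incongruent | Looser reading* |
|---|---|---|---|
| 3 | 0.625 to 0.750 | 1.000 | 0.400 to 0.667 |
| 4 | 0.429 to 0.652 | 0.500 to 0.750 | 0.333 to 0.600 |
| 5 | 0.366 to 0.609 | 0.400 to 0.667 | 0.308 to 0.571 |
| 6 | 0.336 to 0.584 | 0.357 to 0.625 | 0.294 to 0.556 |

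*Previous trial incongruent; colour differs from previous colour, word from previous word, and the trial is not an ignored repetition.

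No reading in this range brings q below 0.29. Requiring an incongruent previous trial, without also requiring an incongruent current one, raises q.

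**Illustration with assumed reaction times.** Let true NP stay at 10 ms and S fall from 100 to 80 ms. With q = 0.5, measured NP goes from 10 + 50 = 60 ms to 10 + 40 = 50 ms. With q = 0.75 it goes from 85 to 70 ms. With q = 0 it stays at 10 ms.

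**The case against.** The strongest reply is that this is a condensed article and its one-line definitions are not a full coding manual. The ignored-repetition sentence on its own would also admit congruent trials, and the restriction comes in a separate sentence. The real trial list may match control trials on congruency, and General Procedure says the tasks were built with counterbalancing and stimulus rotation, so independent random order is a doubtful model. This stands as a limit on size. It does not remove the point, because the authors wrote the restriction for ignored repetition and not for control trials. If the list does match them, only the wording needs correcting.

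The article also codes congruency of the preceding trial in order to compute NP. That may deal with previous-trial effects, so they are not counted against the plan here. It does not deal with congruency of the trial being scored.

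Three stronger readings are tempting and should be resisted.

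- *The two effects cannot be separated.* Too strong. The article also states the aim as a larger effect of training on interference than on NP. With q below 1 and true NP constant, the spurious NP fall is smaller than the Stroop fall, so that ordering survives. The contamination dilutes the predicted contrast; it does not create it.
- *No change in NP will be concluded from a non-significant test.* The article does not say so, and how the contrast is tested is ordinary analysis-plan detail.
- *Specific millisecond errors apply to this trial.* Colours, congruent proportion and reaction times are all unstated.

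**Conclusion.** The concern holds for the coding rule as written. Control trials may be congruent and ignored-repetition trials may not, so measured NP is true NP plus q × S. A training-related fall in Stroop interference would show partly as a fall in NP, against the planned dissociation. Conversely, an NP score that looks unchanged while interference falls could hide a true rise in NP.

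The size is not known. The range of about 0.3 to 0.75 for q, reaching 1 with 3 colours and an incongruent previous trial, rests on assumed random order, 3 to 6 colours and 25 to 50% congruent trials.

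The reach is limited. The Stroop score is unaffected. Randomisation still protects the group comparison of the measured NP score; what is lost is its meaning, because a group difference in NP could not be told apart from one in interference. NP is one component of one of four primary outcome tasks, and the hypotheses in Objectives and Hypotheses do not name it. The point should be corrected before analysis, but it does not threaten the trial as a whole.

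**What to change.** Replace the control rule with: *Control trials are incongruent trials preceded by an incongruent trial, with no overlap between current and previous colour/word.* Then q = 0, and a pure change in Stroop interference leaves the NP score where it was.

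First count the eligible trials per participant and session in the trial list.

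- **Enough trials:** apply the rule. It is a recoding of recorded trials and needs no new data.
- **Too few:** keep control trials incongruent, allow either type of previous trial, and account for previous-trial congruency in the NP model. This still needs some incongruent-after-incongruent control trials across the sample, because ignored-repetition trials occur only after incongruent ones.
- **None:** do not interpret the Stroop-NP dissociation. This is the case with 3 colours, where the factor K − 3 is zero.

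The cost is fewer control trials and a noisier NP score. In the 4-colour example only 29% (p = 0.25) or 9% (p = 0.50) of the present control trials would remain, so 71 to 91% would be dropped. The loss matters more for the ERP averages, which according to Electroencephalograph Acquisition already use only artifact-free correct trials. If the list already matches control trials on congruency, the change is one sentence and costs nothing.

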### Sample Size

The sample size is based on the number of observations needed to compare the 2 groups of gamers, those trained with Lumosity and those trained with The Sims. As we do not have standard deviations of the scores in our main dependent variables, we used G*Power 3.1 (Department of Psychology) to compute the number of participants, using analysis of variance as a statistical test. For this, using a power of .80, effect size of 0.50, an alpha level of .05, and 2 groups within the *F* test family, we obtained a required total sample size of 57. With a dropout rate of 10%, a total of 63 participants would be required. Rounding up the numbers, we would need more than 64 participants (32×2). As the flow diagram shows, the final number of participants matches these a priori computations closely: 38 participants were assigned to the experimental group (8 lost at posttest) and 37 to the control group (12 lost at posttest).

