
### General Procedure

Participants in the study were randomly assigned to the cognitive nonaction video game training group or the noncognitive game training active control group. The introduction of an active control group is necessary to avoid placebo effects [54]. Based on the results of our meta-analytic study [61], we use training regimes that are not too long to avoid loss of motivation, and simple, nonaction games that appeal more to elders. According to the temporal discount hypothesis [85], future rewards are less valuable than inmediate rewards. In each session, the trainees play 10 nonaction video games from Lumosity, described below.

The main question examined in our study is whether group (experimental group, active control group) interacts with testing session (pretest, posttest, and follow-up) with regard to performance on a series of cognitive tasks. At least 2 measures for each cognitive domain are acquired to examine transfer of training to untrained tasks demanding attention and working memory. We selected these cognitive domains because these functions deteriorate with aging and tax functions that are critical for independent living. To explore the underlying neural mechanisms of successful transfer of training gains to attentional mechanisms (alert, distraction, and inhibitory effects) and executive control (spatial working memory), electrophysiological data (ERPs) are recorded at pretraining (T1), posttraining (T2), and 6-month follow-up (T3).

All the methodological designs of the primary outcome measures have been constructed using the rules of counterbalancing and stimulus rotation. Response keys are counterbalanced across conditions. The computerized tasks have been programmed using E-Prime 2.0 (Psychology Software Tools Inc). All the statistical analyses of the behavioral results will be performed using SPSS (IBM Corp) and results will be considered significant at *P*<.05, with Bonferroni-corrected post hoc tests performed as appropriate. Continuous EEG activity are recorded in our laboratory with thin electrodes from 34 scalp sites using a NuAmps amplifier as mentioned before.

After randomization and initial assessment (baseline), participants were invited to attend the University Center of Escuelas Pias in Madrid to perform the training sessions in small groups. Trained and active control groups followed 16 training sessions carried out on different hours and days that lasted approximately 10 to 12 weeks.

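### The stated Stroop and negative priming analyses do not test whether training affects one more than the other, and a non-significant negative priming result cannot show that it is unchanged

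*Protocol article*

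**What the plan says.** All of this is in the protocol article.

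- **Aim, as a comparison** (Stroop and Negative Priming Task, under Primary Outcomes). Training is meant to improve effortful inhibition, measured by Stroop interference, "to a greater extent than automatic passive inhibition (NP").
- **Aim, as an absence of effect** (same section). The question is "whether the Stroop interference effect in older adults decreases after training while NP does not change".
- **Stroop analysis** (same section). "Responses for the Stroop analysis will be coded as a function of the congruency between the color and the meaning of the stimulus".
- **NP analysis** (same section). It has its own factor list: group, session and type of intervention "as between-participants factors and Repetition (ignored repetition and control) as within-participants factors". No factor distinguishes Stroop from NP.
- **Inference** (General Procedure). "results will be considered significant at *P*<.05, with Bonferroni-corrected post hoc tests performed as appropriate".
- **Model** (Results). "Analyses of variance will be conducted with 2 groups (experimental and active control) at 3 time points".
- **Numbers** (Sample Size). 38 and 37 were assigned, and 8 and 12 were lost at posttest.

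The article states no contrast between the two training effects, and no interval or margin for the claim that NP is unchanged.

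**The concern.** The aim makes two claims, and each needs its own inference. That one effect improves more than another is a statement about a difference, so the difference has to be estimated. That NP stays the same is a statement of absence, and P≥.05 cannot establish it.

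The article goes further than leaving detail to an analysis plan. It writes out how each effect will be coded and gives NP a factorial design, and that design cannot answer the question posed. Readers would be left to set one P value beside the other. On that basis the trial could report that training acts selectively on controlled inhibition when both processes had benefited equally. The null half of the aim also rewards imprecision: the noisier the NP score, the more likely it is to appear unchanged.

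**Working it through.** **Inputs from the article.** Posttest numbers are 38 − 8 = 30 and 37 − 12 = 25, giving 30 + 25 − 2 = 53 degrees of freedom. Alpha is .05, taken as two-sided. The article gives no SDs, so effects are in units of the SD of the change score.

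**Assumptions, not in the article.** True standardised benefits equal on Stroop and NP, d from 0.3 to 1.0; correlation of the two change scores (both coded so that positive means benefit) from 0 to 0.7; normal data; a pre-post comparison between arms, which is one component of the planned three-session analysis.

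**The plan's own figure.** There is none for this aim. The sample-size paragraph, "using a power of .80, effect size of 0.50, an alpha level of .05, and 2 groups within the *F* test family", gives a total of 57 for a two-group comparison and does not name the effect-size metric. Read as Cohen's f = 0.5 (d = 1.0), two groups need 34. Read as d = 0.5 (f = 0.25), they need 128. Neither gives 57, which corresponds to f of about 0.38 (d about 0.76). That is a separate matter, but it means the article does not settle which d to use here.

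**Step 1: precision of the NP result.** Half-width = t(.975, 53) × √(1/30 + 1/25) = 2.006 × 0.271 = 0.54 SD. A non-significant interval spans zero and is about 1.09 SD wide, so in at least one direction it reaches 0.54 SD or more. This step needs no assumed effect size or correlation.

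**Step 2: false dissociation under equal benefit.** Power of a single test comes from the noncentral t with noncentrality d/0.271. At correlation 0, the chance that Stroop is significant and NP is not is close to p(1 − p). Correlated cases were simulated.

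| True d, both effects | Power p of one test | p(1 − p), correlation 0 | Range, correlation 0.7 to 0 |
|---|---|---|---|
| 0.3 | 19% | 0.192 × 0.808 = 15.5% | about 8-15% |
| 0.5 | 44% | 0.442 × 0.558 = 24.7% | 13-25% |
| 0.8 | 83% | 0.826 × 0.174 = 14.4% | 8-14% |
| 1.0 | 95% | 0.952 × 0.048 = 4.6% | 3-5% |

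**Step 3: the direct contrast.** Testing the Stroop change minus the NP change between arms falsely favours Stroop in about 2.5% of trials in every setting above.

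**Step 4: what the contrast costs.** Suppose Stroop truly improves by d = 0.5 and NP by 0. The difference of the two changes has SD √(2(1 − ρ)).
- ρ = 0: 0.5/1.414 = 0.354, power 25%.
- ρ = 0.5: 0.5/1 = 0.5, power 44%.

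**Step 5: direction.** The article describes NP as a measure of distractor inhibition. Better inhibition lowers Stroop interference but may enlarge NP. If the raw changes are subtracted without aligning their signs, equal benefits of d = 0.5 add instead of cancelling. The standardised difference is then 1.0/√(2(1 + ρ)), from 0.71 at ρ = 0 to 0.54 at ρ = 0.7. The contrast would be significant in 73% down to 50% of trials although both processes benefited equally.

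**The case against.** **The decision rule.** A reader might infer that the trial will declare the dissociation from one significant and one non-significant P value. The article does not say so. Its P<.05 statements are general, its comparative wording fits a direct contrast, and it gives no factor list for Stroop that would exclude a joint model. An analysis plan that is not shown may contain the test. This stands, so the rates in Step 2 are conditional. What remains is that the analyses the article does state answer neither half of its aim.

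**How often.** A reader might also infer that a false dissociation is frequent at this sample size. That depends on an effect size the article does not fix. If 0.50 is Cohen's f, the rate is 3-5%. Only the range of about 3-25% can be defended. Elsewhere the article describes video game effects in older adults as moderate, and as negligible for executive functions, which does not point to d = 1.0 but does not settle the matter.

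**Simplification.** The calculation is a two-session comparison, whereas three sessions are planned. This also stands; follow-up numbers are not given.

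**Importance.** General Procedure names group by session on task performance as the main question, and the primary outcomes are better performance on each task. Selectivity of Stroop over NP is a sub-aim about mechanism. This stands and limits the weight of the point.

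**The remedy.** A simple contrast of standardised changes has faults of its own: the sign problem in Step 5, and a scale problem, since a noisier NP score has a larger SD and therefore a smaller standardised change, which tilts the contrast towards Stroop. Both are addressed in the fix.

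**Conclusion.** The point holds in a limited form and should be acted on. The stated analyses contain no test of the difference between the Stroop and NP training effects, and a non-significant NP result could not show absence of change: the half-width of ±0.54 SD follows from the posttest numbers alone for a pre-post comparison. If the dissociation were inferred from contrasting significance, the error rate under equal benefit would be about 3-25%, against about 2.5% for a direct contrast. That range rests on assumed equal standardised effects, correlations of 0 to 0.7 and normal data. The two scores share trials, because ignored-repetition trials are always incongruent, so the correlation after aligning directions could even be negative, which the range does not cover. The main group by session efficacy question is not affected.

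**What to change.** 1. State the test of the comparative aim: the group × session (pretest, posttest) × effect type (Stroop, NP) contrast. With follow-up included, this is one component of a 2-df interaction and should be named as the contrast of interest.
2. Fix in advance, for each effect, which direction counts as better inhibition, and code both changes that way.
3. Name the scale in advance: milliseconds as primary, and changes standardised by the pretest SD as a sensitivity analysis.
4. Report the NP group × session estimate with its 95% CI. Replace the claim that NP does not change with that interval, or with wording limited to no evidence of change.

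The cost is one extra contrast on data already being collected, and the article says analysis is still to come. The real price is power: about 25-44% for true effects of 0.5 and 0 at correlations of 0 to 0.5, and lower still if the correlation is negative. The dissociation will be harder to claim, and the report should say that this sample can support it only weakly.
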